### Interim analyses: the Data Monitoring Committee

An independent Data Monitoring Committee (DMC) with established terms of reference and stopping rules will be appointed to review interim data and other evidence (including updated overviews of relevant randomised controlled trials). The DMC will:

• Advise on protocol modifications suggested by investigators or collaborators (e.g. sample size or trial endpoint modifications)

• Assess the impact and relevance of new external evidence

• Assess data quality, including completeness

• Monitor recruitment figures, balance in recruitment by centre and losses to follow-up

• Monitor evidence for treatment harm

• Monitor planned sample size assumptions

• Monitor treatment side-effects and compliance with the treatment regimen

• Recommend that the trial continues to recruit participants or that recruitment should be terminated

An interim analysis will be conducted when outcomes are known for the first 50% of women recruited. The O'Brien-Fleming method[58] will be used to preserve the overall P-value at 0.05; for the interim analysis we will test at P = 0.0031 (z = 2.95430) and for the final analysis at P = 0.0497 (z = 1.96257) (these calculations were performed using PASS).

The DMC will inform the Steering Group if in their view an arm of the study is either clearly indicated or contra-indicated. The final decision on whether to stop the trial will rest with the Steering Group.

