### Sample size

A sample size of 3,208 women with *Candida *colonisation (1,604 per arm of the trial) is required to detect a 40% reduction in spontaneous preterm births (compared with term birth) among women with asymptomatic candidiasis from 5.0% in the control group to 3.0% for those women treated with clotrimazole (significance 0.05, power 0.8). This is a more conservative risk reduction than that found in the trial by Kiss [14], where analysis of this subgroup suggested treatment of asymptomatic candidiasis was associated with a 65% reduction in spontaneous preterm birth but the numbers were small and the subgroup analysis was post-hoc.

Recruitment of 3,208 women will require 16,040 women to be screened based on a *Candida *carriage rate of 20%. In our pilot study the *Candida *carriage rate was 19.6% and the participation rate among eligible women was 64%. If a participation rate of 64% could be maintained across all participating centres, ~25,000 would need to be approached to achieve screening of 16,040 women. A lower participation rate means more women would need to be approached. We expect that a participation rate of at least 60% could be maintained across all centres and this would mean approaching ~26,000 women.

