### Analyses

Analyses will be by intention to treat. The primary analysis will compare the proportions of spontaneous preterm births in the two groups, using a chi-squared test. The relative risk and 95% confidence interval of preterm birth and other outcomes in women with active treatment compared with those with usual care will be calculated. In the secondary analysis of the primary outcome, logistic regression will be used to adjust for centre and any differences in important baseline characteristics. Secondary outcomes that are binary will be analysed in a similar manner, while those that are quantitative will be compared between groups using t-tests or the distribution-free equivalent, as appropriate.

Sub-group analyses will be used to explore associations between preterm birth and clotrimazole treatment by degree of *Candida *colonisation (light, moderate, heavy), *Candida albicans *and *non-albicans *species, gestational age at enrolment, and among medically indicated preterm births by indication (hypertension, growth restriction, fetal malformation, placental abnormalities). To test for differences in the effect of clotrimazole among sub-groups, a chi-squared test for interaction will be used, using the trend version for the ordered variable, degree of colonisation.

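### The printed O'Brien-Fleming thresholds spend 0.0507, not 0.05: with the stated interim bound at 50%, the final threshold should be P = 0.0490, not 0.0497

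*Protocol article*

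**What the plan says.** The section on interim analyses and the Data Monitoring Committee (DMC) sets one look: "An interim analysis will be conducted when outcomes are known for the first 50% of women recruited". It names the method, "The O'Brien-Fleming method[58] will be used", and its purpose: the method "will be used to preserve the overall P-value at 0.05". It then gives the two thresholds, interim first: "we will test at P = 0.0031 (z = 2.95430) and for the final analysis at P = 0.0497 (z = 1.96257". The calculation is credited to a commercial sample-size package.

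The Analyses section makes the primary analysis a comparison of the two proportions "using a chi-squared test". The Sample size section gives 1,604 women per arm to detect a fall "from 5.0% in the control group to 3.0% for those women treated with clotrimazole (significance 0.05, power 0.8".

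**The concern.** In a two-look design, the timing of the look and the two bounds together fix the overall type I error. The article states all three and also states the result, 0.05, so the claim can be checked without any outside figure.

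The final threshold looks too lenient on its face. The interim test spends 0.0031, yet the final threshold falls by only 0.0003 below 0.05. That small a reduction would be enough only if almost every trial that crossed at the interim would also cross at the end. At half the information, the two statistics are not correlated strongly enough for that.

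The final threshold decides whether the primary result of a trial meant to be definitive is called significant. If the number is carried into an analysis plan or a DMC charter, the mismatch goes with it, and it can be corrected without dispute only before outcome data are seen.

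**Working it through.** **Inputs, all from the article.** Look at information fraction t = 0.5; interim bound c1 = 2.95430; final bound c2 = 1.96257; target overall error 0.05. The text does not state sidedness, but the z-to-P pairs settle it.

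**Step 1: does each P match its z?** P = 2[1 − Φ(z)].
- Interim: 2[1 − Φ(2.95430)] = 0.00313, printed as 0.0031.
- Final: 2[1 − Φ(1.96257)] = 0.04970, printed as 0.0497.

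Both agree, so the tests are two-sided and there is no misprint within either pair.

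**Step 2: overall error of the pair.** Under the null, Z1 and Z2 are bivariate standard normal with correlation √t = √0.5 = 0.7071.

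Overall error = 1 − P(|Z1| < c1 and |Z2| < c2)

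- Spent at the interim: 0.00313
- Added at the final analysis (not crossed at the interim, crossed at the end): 0.04759
- Total: 0.00313 + 0.04759 = **0.05072**

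Equivalently, the two single-test errors sum to 0.00313 + 0.04970 = 0.05283, and the chance of crossing both bounds is 0.00211, so 0.05283 − 0.00211 = 0.05072. A simulation of 40 million draws gave 0.05074 (standard error 0.00003). Using the rounded P-values in place of the z-values gives 0.05071, so rounding is not the cause.

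**Step 3: final bound that gives exactly 0.05.** Holding c1 = 2.95430 and solving 1 − P(|Z1| < 2.95430 and |Z2| < c) = 0.05 gives c = 1.9689, P = 0.0490.

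**Step 4: does any standard version give the printed pair at t = 0.5?**

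| Boundary | Interim z (P) | Final z (P) | Overall error |
|---|---|---|---|
| As printed | 2.954 (0.0031) | 1.963 (0.0497) | 0.0507 |
| Classical O'Brien-Fleming | 2.797 (0.0052) | 1.977 (0.0480) | 0.0500 |
| Lan-DeMets, O'Brien-Fleming-type spending | 2.963 (0.0031) | 1.969 (0.0490) | 0.0500 |
| Printed interim, final solved | 2.954 (0.0031) | 1.969 (0.0490) | 0.0500 |

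The printed interim P agrees with the Lan-DeMets version to four decimals. The printed final value matches neither version. Lan-DeMets spending does return the printed pair (2.9543 and 1.9626) if the total error is set to about 0.0507. That may point to the input used, but it is only an inference.

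**Step 5: would other timing rescue the pair?** Overall error of the printed bounds by information fraction: 0.0511 at 40%, 0.0507 at 50%, 0.0503 at 60%, 0.0500 at 70%, 0.0498 at 80%. The pair holds 0.05 only from about 70% information onwards, and the article fixes 50%.

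**Step 6: power of the corrected threshold.** For 1,604 per arm, 5.0% against 3.0%, taking the final test alone:
- Uncorrected chi-squared: 82.4% at z = 1.96257, 82.2% at z = 1.9689.
- Continuity-corrected: 79.9% at z = 1.96257, 79.7% at z = 1.9689.

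The stated sample size itself reproduces with the continuity correction at alpha 0.05 (1,605 after rounding up, against 1,604).

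**The case against.** The arithmetic is not in dispute; its importance is. There are four arguments.

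1. **The excess is tiny.** It is 0.0007, and 0.0507 still rounds to 0.05. Only a final P between 0.0490 and 0.0497 would be judged differently. This stands as a statement of practical effect.

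2. **The normal approximation is itself this inexact.** Exact binomial enumeration of a single final test at z = 1.96257, with 1,604 per arm, gives a size for the uncorrected chi-squared test of 0.0492, 0.0494 and 0.0497 at common rates of 3%, 4% and 5%. With a continuity correction the size is about 0.039 to 0.041, and the article does not say which version will be used. So the true error of the test as run may be at or below 0.05. This is correct, but it does not validate the boundary: group-sequential bounds are set on the normal scale, and on that scale the claim fails.

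3. **Stopping is not automatic.** The DMC advises and the Steering Group decides. If an interim crossing were ignored and only the final test counted, the error would be 0.0497, so 0.0507 is the figure for a rule that is followed. That is still the right check for a design claiming control of the overall error.

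4. **The power cost depends on the formula.** With the continuity correction that reproduces the sample size, power is already a shade under 80% at the printed threshold. The change costs about 0.2 points under either formula, so this is not a reason to keep the wrong threshold.

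It is also fair to say that naming the spending function and recalculating at the realised information fraction could be left to an analysis plan. The printed final threshold cannot, because the article fixes it.

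**Conclusion.** The concern holds. As printed, the two thresholds with one look at 50% information give an overall two-sided type I error of 0.0507, and the statement that 0.05 is preserved is incorrect. The final threshold is too lenient by 0.0497 − 0.0490 = 0.0007.

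This rests on the stated 50% timing being the information fraction, on the usual joint normal distribution of the two test statistics, and on an interim crossing counting as a rejection. No standard O'Brien-Fleming variant at that timing yields the printed pair with a total of 0.05. The practical effect is minor and the design is otherwise untouched, but this is the pre-specified threshold for the primary test and should be right before any outcomes are examined.

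**What to change.** Rerun the boundary calculation with a total two-sided alpha of 0.05 and one look at 50%. Keep the interim threshold at about P = 0.0031 and replace the final one with P = 0.0490 (z = 1.969). State that the bounds come from an O'Brien-Fleming-type (Lan-DeMets) spending function, and that the final bound will be recomputed from the information fraction actually reached at the look. The new threshold is the essential part; naming the function is secondary, but it removes the ambiguity with the classical boundary, whose thresholds differ (P = 0.0052 and 0.0480).

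The cost is one sentence and one rerun. The planned 1,604 per arm can stay: the power loss is about 0.2 percentage points (82.4% to 82.2% uncorrected; 79.9% to 79.7% with continuity correction).

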### Ethics Approval

Ethics approval has been granted by the Northern Sydney Central Coast Area Health Human Research Ethics Committee (Protocol 0907-165M)

## Discussion

Prevention of preterm birth remains one of the most important challenges in modern maternity care. Providing *a Healthy Start to Life*, an Australian National Research Priority, is the goal of this proposal. This trial will provide definitive evidence on whether screening and treating of asymptomatic candidiasis in pregnancy significantly reduces the rate of spontaneous preterm birth. A significant reduction in preterm birth would have major resource implications with a commensurate reduction in the need for neonatal facilities, hospitalisations and longer term care for babies born preterm.
